**3.7. Follow-up of patients**

**Table 2 : Timetable of activities during the study**

| **ACTIVITIES** | **D1** | **D2-11** | **D12** | **M6** | **M12** | **M24** | **Non-scheduled days** |
| --- | --- | --- | --- | --- | --- | --- | --- |
| **Informed consent– Inclusion** | X |  |  |  |  |  |  |
| **Randomisation** | X |  |  |  |  |  |  |
| **Clinical evaluation** | X | X | X | +/- | +/- | +/- | +/- |
| **Parasitological evaluation**  Woo  QBC  GP  LP | X  X  +/-  X |  | X  +/-  X | X  +/-  X | X  +/-  X | X  +/-  X | X  +/-  X |
| **Biological evaluation**  CSF white cells counts  Haematocrit Y  WBC count Y  Differential count Y | X  X  X  X |  | X  X  X  X | X | X | X | X |
| **Sampling for Antwerp study**  CSF sample collection  Serum sample collection | X  X |  | X  X | X  X | X  X | X  X | X  X |
| **Treatment**  Prednisolone *  A : Melarsoprol+nifurtimox  B : Melarsoprol+eflornithine  C : eflornithine +nifurtimox | X | X  X  X  X |  |  |  |  |  |
| **New therapeutic scheme if treatment failure** |  |  | X | X | X | X | X |

Y Only for the first 50 subjects

* Only for treatments A or B

## Follow-up duration

Patients included in the study will be monitored for 24 months after the end of treatment.

Laboratory tests (lumbar puncture, glandular puncture, QBC, haematology) and clinical examinations will be undertaken at the end of hospitalisation and 6, 12 and 24 months after the end of the treatment.

A network of community health workers will ensure the presence of the patients included in the study at the 3 scheduled follow-up visits as far as possible. In addition, the address of each patient included in the study will be noted at the time of admission. Anyone missing a follow-up visit will be sent a reminder 3 times.

Apart from this, the patient will be allowed to come at any time in the trypanosomiasis treatment centre throughout the follow-up period.

***Lost to follow-up***

A active follow-up programme will be implemented in order to limit the proportion of lost to follow up. Any patient failing to come back for control will be contacted by a special mobile team and asked to come to the treatment centre for control.

A patient will be declared a "drop-out" if he/she misses the 24-month follow-up visit.

***Classification of responses to treatment***

**Table 2**: **Classification of responses to treatment**

| 1. **A patient will be considered « cured » at a control visit at 24 months if THE TWO following conditions are fulfilled:**    Trypanosomes are absent from blood and CSF (and from gland juice if adenopathy)   CSF contains <20 cells per mm3 |
| --- |
| 1. **A patient will be considered as « treatment failure » if at a control visit at 24 months the patient presents with ONE of the following criteria:**  - Trypanosomes are present in blood (or in gland juice if adenopathy) with any cell count in CSF - rypanosome are present in CSF with any cell count in CSF - Cell count in CSF is ³20 cells per mm3 |
| 1. **A patient will be considered as «treatment failure» at any control visit if ONE of the following conditions is fulfilled:**  - Trypanosomes are present in blood (or in gland juice if adenopathy) with any cell count in CSF - Trypanosomes are present in CSF with any cell count in CSF - Cell count in CSF is ³20 cells per mm3, and has increased since the end of treatment - Cell count in CSF is ³ 20 cells per mm3, and has increased two times consecutively |
| 1. **A patient will be considered « to be seen at three months » at any control visit if THE TWO following conditions are fulfilled:**  - Trypanosomes are absent from blood and CSF (and from gland juice if adenopathy) - Cell count in CSF is ³ 20 cells per mm3, and has increased since the last control visit |

If a patient is not in accordance with these definitions, the final decision will be left to the clinical staff in charge.

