## Blind

The modes of administration of melarsoprol (direct IV), nifurtimox (orally) and eflornithine
(2-hour infusion) are different. A blind study is therefore not readily feasible under field conditions.

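### Two rows of the response table overlap with no order of precedence, so the same CSF counts can mean both treatment failure and recall at three months

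*Protocol*

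**What the plan says.** Table 2 in protocol section 3.7 (Classification of responses to treatment) has four rows.

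- **Row 1, cured at month 24:** no trypanosomes and fewer than 20 CSF cells per mm3.
- **Row 2, failure at month 24:** trypanosomes present, or 20 or more cells.
- **Row 3, failure** "at any control visit if ONE of the following conditions is fulfilled": trypanosomes are not required. One sufficient condition is a count of 20 or more "cells per mm3, and has increased since the end of treatment". Another is a count of 20 or more after two consecutive rises.
- **Row 4, recall:** "A patient will be considered « to be seen at three months » at any control visit if THE TWO following conditions are fulfilled". The two conditions are absence of trypanosomes, and a count of 20 or more "and has increased since the last control visit".

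The closing sentence reads: "If a patient is not in accordance with these definitions, the final decision will be left to the clinical staff in charge".

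Under Follow-up duration, laboratory tests and clinical examinations "will be undertaken at the end of hospitalisation and 6, 12 and 24 months after the end of the treatment".

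Section 3.8 makes the proportion of therapeutic failures the first outcome variable. It also reads the relative hazard as the risk of treatment failure. Section 3.7 prescribes re-treatment for failures, with one regimen for groups A and B and another for group C. On masking, section 3.6 states: "A blind study is therefore not readily feasible under field conditions".

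**The concern.** Rows 3 and 4 apply at the same visits, use the same threshold of 20 cells and differ only in the earlier value used for comparison. A count above both earlier values satisfies both rows, and the table does not say which one governs.

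The two classes lead to different courses. A failure is counted in the primary outcome, is an event in the survival analysis and is re-treated. A recalled patient goes on being observed and can still be classed as cured at month 24. The classes are applied in the field during follow-up, by staff who can know the arm. The same laboratory results could therefore be handled differently from patient to patient, or from arm to arm.

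**Working it through.** There is no figure in the plan to reproduce; this is a check of logic. The inputs are the four rows of the table and the visit schedule (D12, month 6, month 12, month 24). All cases below are trypanosome-free. Write E for the end-of-treatment count, L for the count at the last control visit and C for the current count.

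- Row 3 by count: C ≥ 20 and C > E, or C ≥ 20 after two consecutive rises.
- Row 4: C ≥ 20 and C > L.
- Both rows hold whenever C ≥ 20 and C exceeds both E and L.

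**Month 12** (E at D12, L at month 6)

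| D12 | M6 | M12 | Row 3 | Row 4 |
|---|---|---|---|---|
| 10 | 15 | 25 | yes (25 > 10) | yes (25 > 15) |
| 100 | 30 | 60 | no (60 < 100, one rise only) | yes (60 > 30) |
| 100 | 30 | 25 | no | no |

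Take all count triples from 0 to 100 in steps of 5, and write C = 5k with k = 4 to 20.

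- Row 4 leaves k choices for L and 21 for E: 21 × (4 + 5 + … + 20) = 21 × 204 = 4284 triples.
- Requiring also C > E leaves k choices for E: 4² + 5² + … + 20² = 2856 triples.
- So 2856 of the 4284 triples that meet row 4 also meet row 3. Row 4 stands alone only when the count fell after treatment and then rose without passing E.

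These are counts of possible combinations, not expected patient frequencies.

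**Month 6.** The result depends on whether D12 is a control visit.

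- If it is, and there was no unscheduled visit in between, then L = E and the two count conditions are identical. Over counts 0 to 100, the pairs meeting row 4 number 20 + 21 + … + 100 = 5050 − 190 = 4860, and all 4860 also meet row 3 (for example 10 then 25).
- If it is not, row 4 has no scheduled reference value at month 6.

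The protocol points both ways. Follow-up duration counts three scheduled follow-up visits, which suggests that D12 is not one. Yet the timetable of activities marks D12 as a point at which a failure can be given new treatment.

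**Month 24.** Counts 100, 30, 25, 60 at D12, month 6, month 12 and month 24 give:

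- Row 2: failure, since 60 ≥ 20.
- Row 3: not met, since 60 < 100 and there was only one rise.
- Row 4: met, since 60 > 25.

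So row 4 collides with row 2 even where row 3 does not apply.

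**Effect on the endpoint.** Suppose the patient with 10, 15, 25 is recalled rather than failed. If the month-24 count is 20 or more, row 2 makes the patient a failure anyway. The final status differs only if the patient is later trypanosome-free with fewer than 20 cells at month 24. With the planned 130 patients per group, each such patient is 1/130 = 0.77 percentage points of an arm's failure rate. The date of failure can differ even where the final status does not.

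**The case against.** **A coherent failure-first reading exists.** Row 4 then keeps the cases in which the count fell and rose again without passing the end-of-treatment value (100, 30, 60), and the two-consecutive-rises condition in row 3 deals with a further rise. Failure is an outcome, whereas row 4 is a recall instruction. This is a sensible reading, but the table does not state it. The two-rises condition can equally be read as meaning that one rise prompts a recheck and a second means failure.

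**A reader might infer that every patient with 20 or more cells and a rise at month 6 is classed twice.** That holds only if D12 is a control visit and no unscheduled visit came between. The overlap at month 12 does not depend on this.

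**A reader might infer that the protocol hands the choice to unblinded clinicians.** The closing sentence covers patients who fit none of the definitions, not those who fit two. The cell counts are also duplicated, with a third count when they disagree, and recorded under a patient code (section 5.2). What stands is that no rule resolves the double fit and that the trial is open. Biased choice by arm is a possibility, not something the text provides for.

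**A reader might want a larger size**, for example five patients moving the difference by 5/130 = 3.8 points and so using up the room for equivalence. Five is hypothetical, and not every reclassified patient changes status. The comparison is also loose. Using the variance at 95% and 85% cure, the largest observed difference that passes is about 3.96 points. Yet 124 against 118 cured of 130, a difference of 4.6 points, has an upper limit of 9.77 and still passes.

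**Derivation programs and sensitivity analyses usually belong in the SAP.** Agreed, and their absence is not criticised here. The point is that the protocol itself fixes two rules that conflict and that act during follow-up.

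**Conclusion.** The contradiction is real. Rows 3 and 4 give one patient two classes at month 12 on any reading of the control-visit term, and rows 2 and 4 do so at month 24. At month 6 the rows either coincide or row 4 lacks a scheduled reference value, depending on how D12 is read. Because the failure class is the first outcome variable, enters the survival analysis and triggers re-treatment, this is a defect in the definition of the primary endpoint and not a missing detail.

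Its size cannot be stated. The final status changes only for patients who would later be trypanosome-free with fewer than 20 cells at month 24, at 0.77 points each on the assumption of 130 analysed per arm. The protocol gives no basis for their number. It does not support a claim that all patients with a rise at month 6 are affected, that clinicians are assigned the choice, or that the equivalence conclusion would be overturned.

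**What to change.** The sponsor must reconcile rows 2, 3 and 4 so that the classes are mutually exclusive, either by one stated order of precedence or by changed conditions. The text should also say whether the D12 examination counts as a control visit. Which clinical rule applies is the sponsor's decision.

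For the analysis, apply the reconciled rule to the laboratory results already held under patient codes (section 5.2), without reference to arm.

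A sensitivity analysis under the other precedence is possible but should be described as limited: once a patient has been re-treated as a failure, the later course without re-treatment is not observed.

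The cost is a short amendment to the table, a matching change to the field guideline and a brief derivation. If precedence alone is stated, no scheduled visits are added. Because the class triggers re-treatment, the wording should be settled before follow-up visits begin.

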**3.8. Analysis**

This will be an "intention-to-treat" analysis. The treatment groups will be compared pair-wise.

The first outcome variable is the proportion of therapeutic failures in each treatment group.

The second outcome variable is the proportion of side effects occurring in each group.

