**5. Control of bias and quality control procedures**

**5.1. Bias control**

The randomisation process prevents the introduction of any bias in selection by the care teams when patients are included. However, the lack of blinding does not guarantee uniform treatment of the patients among the 3 groups.

The blocking technique used for the randomisation prevents any imbalance over time in the distribution of the number of patients between the 3 groups that might have been the source of a bias in selection. This process will only be known to the medical personnel at the end of the inclusion period.

Treatment compliance must be guaranteed by the admission of all patients to the treatment centre.

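### In this open trial, staff who know the arm settle the outcome of patients who fit no row of the response table; the routes into the primary endpoint are few, but a failure called this way is re-treated and month 24 cannot correct it

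*Protocol*

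**What the plan says.** The summary of methods bases the assessment on trypanosomes in CSF, blood or lymph node fluid and on the spinal cell count. Section 3.8 then states: "The first outcome variable is the proportion of therapeutic failures in each treatment group".

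The response table in section 3.7 has four rows:

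- **Cured**, at month 24 only: no trypanosomes, and "CSF contains <20 cells per mm3".
- **Failure at month 24**, which applies "if at a control visit at 24 months the patient presents with ONE of the following criteria": trypanosomes present, or 20 or more cells.
- **Failure at any control visit**: trypanosomes present; or 20 or more cells with an increase since the end of treatment; or 20 or more cells with two consecutive increases.
- **Three-month review**, at any control visit: no trypanosomes, and 20 or more cells with an increase since the last control visit.

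The closing sentence reads: "If a patient is not in accordance with these definitions, the final decision will be left to the clinical staff in charge".

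On blinding, section 3.6 concludes: "A blind study is therefore not readily feasible under field conditions". Section 5.1 concedes that "the lack of blinding does not guarantee uniform treatment of the patients among the 3 groups". Blind reading appears only in section 5.2, for duplicate laboratory samples. Patients identified as failures during follow-up receive a different treatment combination (section 3.7). A patient who misses the month-24 visit is a drop-out (section 3.7, Lost to follow-up).

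**The concern.** The closing sentence sets no criterion, no documentation requirement and no limit. The people deciding are those giving an open treatment. Section 1.2 reports that about 25% of first melarsoprol courses in Arua fail, and melarsoprol is in groups A and B but not C. The threshold for calling an ambiguous finding a failure could therefore plausibly differ between arms, although the protocol cannot show that it would, or in which direction.

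The two possible errors are not symmetric. If staff hold back from calling a failure at month 6 or 12, the patient goes on to month 24 and is classified there by rule. If they do call one, the patient is re-treated and the month-24 findings no longer reflect the allocated combination. That call then stands in the primary proportion and in the failure-free survival analysis.

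**Working it through.** **1. Which patients have no row?** Each combination of findings was set against the four rows. At month 6 the end-of-hospitalisation examination is taken as the last control visit (an assumption), so the two comparisons for an increase coincide there.

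| Finding | Month 6 or 12 | Month 24 |
|---|---|---|
| Trypanosomes present | failure | failure |
| Absent, under 20 cells | **no row** | cured |
| Absent, 20 or more, no increase on either comparison | **no row** | failure |
| Absent, 20 or more, increase since last visit only | three-month review (month 12 only) | failure and three-month review |
| Absent, 20 or more, increase since end of treatment only | failure (month 12 only) | failure |
| Absent, 20 or more, increase on both | **failure and three-month review** | failure and three-month review |

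At the scheduled month-6 and month-12 visits, two consecutive increases after treatment imply an increase since the end of treatment, so that criterion adds no further case.

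**2. Which of these reach the endpoint?** At month 24 the cured and failure rows are exact complements, so any complete examination yields a result. Three routes remain:

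- trypanosome-negative at month 6 or 12 with 20 or more cells that have not increased (for example 200 at the end of treatment and 60 at month 6);
- clinical suspicion of relapse with fewer than 20 cells before month 24;
- attendance at month 24 with an incomplete examination, for example no lumbar puncture. That is not a missed visit, so the drop-out rule does not apply, and the patient may fit no row.

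**3. The plan's sample size** (section 3.3: 95% cure, 10-point difference, one-sided 5%, power 80%). Comparing 95% with 85%:

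- n = [1.645 × √(2 × 0.90 × 0.10) + 0.842 × √(0.95 × 0.05 + 0.85 × 0.15)]² / 0.10² = 110.2, that is 111.
- With continuity correction: (110.2/4) × [1 + √(1 + 4/(110.2 × 0.10))]² = 129.5, that is 130.
- With 10% drop-out: 130/0.90 = 144.4, that is 145 per group, and 3 × 145 = 435.

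The stated figures reproduce, and this point does not alter them.

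**4. How many extra failures matter?** Section 3.8 uses the upper limit of the 90% interval (one-sided 95%) against 10%. With n = 130 per arm and failure proportions a and b:

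upper limit = (b − a) + 1.645 × √[a(1 − a)/n + b(1 − b)/n]

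At 95% cure, 0.05 × 130 = 6.5 failures are expected, so both 6 and 7 were used as the starting count.

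| Failures, arm 1 v arm 2 | Difference (points) | Upper limit |
|---|---|---|
| 6 v 6 | 0.00 | 4.28% |
| 6 v 10 | 3.08 | 7.97% |
| 6 v 12 | 4.62 | 9.77% |
| 6 v 13 | 5.38 | 10.67% |
| 7 v 7 | 0.00 | 4.60% |
| 7 v 12 | 3.85 | 9.14% |
| 7 v 13 | 4.62 | 10.03% |

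Example, 6 v 13: a = 0.0462, b = 0.1000, standard error = √(0.000339 + 0.000692) = 0.0321, so the limit is 0.0538 + 1.645 × 0.0321 = 0.1067.

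Each extra failure moves the difference by 1/130 = 0.77 points. Four extra failures leave the equivalence conclusion in place; six (from 7) or seven (from 6) overturn it.

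**The case against.** The strongest reply is that a visit without a row is not an undecided endpoint. A reader might infer that, because the commonest month-6 and month-12 finding (no trypanosomes, fewer than 20 cells) has no row, the primary endpoint is broadly open to discretion. The protocol does not support that. Such a patient normally continues to month 24, where the rule classifies everyone fully examined. The closing sentence also speaks of a patient, not a visit.

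A reader might also infer that staff settle the planned drop-outs (0.10 × 145 = 14.5 per arm). The protocol labels anyone who misses month 24 a drop-out and includes drop-outs in the Kaplan-Meier analysis. How they count in the primary proportion may properly sit in an analysis plan that is not shown. They do not belong in the size of this point.

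Two smaller replies are fair. Section 5.1 concedes unequal treatment, not unequal classification. The closing sentence could also be meant for care only. But it stands under a heading on classifying response and nothing confines it to care.

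The three narrow routes survive these replies. Nor is this a detail for the analysis plan: the protocol itself fixes the classification rule, and no later analysis can undo re-treatment given under it.

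**Conclusion.** The concern holds in a limited form and should be acted on. Arm-aware judgement can enter the primary endpoint through the three routes above. When it produces an early failure call, that call is irreversible.

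The number of patients affected is unknown, because the protocol gives no interim cell counts. The 6 to 7 extra failures are a sensitivity figure, not a forecast. It assumes 130 evaluable per arm, about 95% cure in the comparison arm, a Wald limit, and all the extra failures falling in one arm.

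Separately, a trypanosome-negative patient with 20 or more cells, increased since both the end of treatment and the last visit, meets the failure row and the three-month row together. At month 6 this covers every patient in the three-month row, on the assumption stated above. That conflict lies outside the closing sentence, which covers patients who fit no row rather than two, but it leaves the same staff to choose.

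**What to change.** For endpoint purposes only, leaving care to the clinicians:

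1. Add an interim class, *no failure so far, continue follow-up*, for any visit before month 24 that meets neither a failure row nor the three-month row.
2. Record a failure declared on any other ground as *clinician-declared failure*, with the laboratory values at that visit.
3. Do not count a patient re-treated on that basis as cured from a later month-24 result. Simply dropping these failures from the primary proportion would let re-treatment produce apparent cures and favour equivalence.
4. By the same logic, record an incomplete month-24 examination that meets no failure criterion as having no month-24 result, unless a failure is declared under item 2.
5. Analyse the primary proportion twice: with clinician-declared failures counted as failures, and with laboratory-defined failures only. In the second analysis, re-treated patients without a laboratory failure have no month-24 result. Claim equivalence only if both agree.
6. Reconcile the overlap between the any-visit failure row and the three-month review row, so that one finding leads to one class.

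The cost is a few sentences under the response table, one case report form code, one added analysis and a slightly stricter equivalence claim. The sample size calculation is unchanged.

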***Decisions in the event of trypanosomiasis infection during the follow-up:***

- *For the first-stage of T.b. gambiense infection*

Patients from any groups identified positive for first-stage *T.b. gambiense* infection will be treated with pentamidine by current protocol (4 mg/kg/day during 10 days).

- *For second-stage of T.b. gambiense infection or treatment failure*

Patients from groups A and B identified as therapeutic failures will be treated with the following protocol: [eflornithine at 400 mg/kg/day for 14 days + nifurtimox at 15 mg/kg/day for 14 days]. Patients from group C identified as therapeutic failures will be treated with the following  protocol: [eflornithine with 400mg/kg/day for 14 days + melarsoprol with 2.2 mg/kg/jour for 10 days].

